## Abstract

**Background:**

Pyrethroid-PBO nets have demonstrated improved impact against clinical malaria transmitted by pyrethroid resistant mosquito vectors and are being scaled up across Africa. However very little is known about their physical and insecticidal durability under operational conditions. This study will investigate the attrition, fabric integrity, insecticide content and bioefficacy of DuraNet® Plus, a new WHO prequalified alphacypermethrin and PBO incorporated net developed by Shobikaa Impex Private Limited over 3 years of field use in communities in Benin, Cameroon and Tanzania.

**Methods:**

The study will be conducted in parallel in selected villages in Zakpota District in Benin, Mbalmayo, District in Cameroon and Muheza District in Tanzania. In each country, ~ 1800 households will be recruited and randomised to receive DuraNet® Plus or DuraNet® (a WHO prequalified alphacypermethrin-only ITN). Follow up surveys will be performed at 1 month post distribution to investigate adverse events and subsequently every 6–12 months to assess ITN attrition and fabric integrity following standard WHO procedures. A second cohort of nets will be withdrawn every 6–12 months and assessed for alpha-cypermethrin and PBO content and for entomological activity in laboratory bioassays (cone bioassays and tunnel tests). Alpha-cypermethrin bioefficacy will be monitored using the susceptible Anopheles gambiae Kisumu strain in cone bioassays while PBO bioefficacy will be monitored using pyrethroid resistant strains with overexpressed P450 enzymes in tunnel tests to determine the proportion of efficacious nets (≥ 95% knockdown, ≥ 80% mortality or ≥ 90% blood feeding inhibition in tunnels) at each time point. Nets withdrawn at 12, 24 and 36 months from each country will also be tested in experimental hut trials against wild free-flying pyrethroid resistant Anopheles gambiae sl in Côvè Benin to investigate the superiority of DuraNet® Plus over DuraNet® at each time point under semi field conditions.

**Conclusion:**

This large-scale multi country trial will provide useful information on the durability of a pyrethroid-PBO net (DuraNet® Plus) in 3 different regions in sub-Saharan Africa. The methods proposed for bioefficacy testing could also contribute towards the development of new standardised guidelines for monitoring the insecticidal efficacy of pyrethroid-PBO nets under operational conditions.

## Background

Insecticide treated nets (ITNs) contributed > 80% to the decline in malaria burden observed in endemic countries between the years 2000 and 2015 [1]. However, progress against malaria has stalled in recent years attributable to several factors including the increasing intensity of resistance to pyrethroids; the insecticide of choice used on ITNs [2, 3].

Pyrethroid-piperonyl butoxide (pyrethroid-PBO) ITNs were developed to help maintain the effectiveness this intervention against malaria vectors that have developed resistance to pyrethroids [4]. The PBO component of the net inhibits the activity of mosquito enzymes that metabolise pyrethroids resulting in higher levels of mosquito mortality with pyrethroid-resistant mosquitoes. Community randomized-controlled trials in East Africa, have demonstrated an improved epidemiological impact against clinical malaria in communities receiving pyrethroid-PBO nets compared to standard pyrethroid-only nets [5, 6]. Based on these findings, and several experimental hut trials across Africa, the World Health Organisation (WHO) issued a conditional recommendation for their deployment in areas where vectors have developed resistance to pyrethroids [7]. This has been followed by an increased uptake of pyrethroid-PBO nets across Africa in recent years [8].

To be considered long-lasting, new ITNs are expected to demonstrate physical and insecticidal durability under operational conditions lasting at least 3 years [9–11]. Recent modelling studies have however estimated a much shorter median ITN retention time of 1.64 years across Africa [12]. ITN durability is also reported to vary from one community to another influenced by several location specific factors including, usage by householders, perceived efficacy, fabric integrity, environmental conditions etc. [11, 13]. While the WHO has recommended standardised procedures for assessing the attrition, fabric integrity, insecticidal content and bioefficacy of ITNs over 3 years of community use [9, 11], there is very limited information on the durability of pyrethroid-PBO ITNs. This is partly attributable to the fact that existing WHO ITN durability guidelines were largely tailored towards pyrethroid-only nets. Effective assessment of the durability of pyrethroid-PBO ITNs will require the development of suitable standardised methods and procedures for monitoring the bioefficacy of both active ingredients on these nets over years of field use.

DuraNet® Plus is an alphacypermethrin and PBO incorporated polyethylene net developed by Shobikaa Impex Private Limited. It was recently added to the WHO list of prequalified ITNs [14] based on its improved performance compared to pyrethroid-only nets in experimental hut trials conducted across sub-Saharan Africa (unpublished data). To facilitate programmatic and procurement decisions around the uptake of pyrethroid-PBO nets for malaria control, studies comparing the durability of DuraNet® Plus and other PBO nets to standard pyrethroid-only nets are necessary. This protocol describes a two-arm trial to evaluate the durability of DuraNet® Plus in terms of survivorship, fabric integrity, chemical content, bioefficacy, and user acceptance under field conditions in communities in Benin, West Africa, Cameroon, Central Africa, and Tanzania, East Africa, compared to DuraNet®, a WHO prequalified alpha-cypermethrin ITN. The study will be conducted in accordance with existing WHO guidelines for the evaluation of the durability of ITNs under community use [9] with modifications to enable assessment of the insecticidal durability of the PBO component of DuraNet® Plus.

## Study aims

### Overall aim

To assess the physical and insecticidal durability of an alpha-cypermerthrin and PBO ITN (DuraNet® Plus®) compared to a standard alphacypermethrin only net (DuraNet®) over 3 years of operational use in communities in Benin, Cameroon and Tanzania.

### Secondary aim

▪ To determine the survivorship and fabric integrity of DuraNet® Plus net compared to a standard alpha-cypermethrin-only net (DuraNet®) over 3 years of household use in Benin, Cameroon and Tanzania.▪ To investigate insecticidal activity and chemical content of DuraNet® Plus net compared to DuraNet® over 3 years of household use in Benin, Cameroon and Tanzania.▪ To document adverse events, community perception and user-acceptability of DuraNet® Plus and DuraNet® over 3 years of household use in Benin, Cameroon and Tanzania.▪ To investigate ITN washing habits and washing frequency over 3 years of household use in Benin, Cameroon and Tanzania.

## Materials and methods

### Study arms

This study consists of two arms evaluating the durability of DuraNet® Plus compared to DuraNet® A description of the two ITN types is provided below:DuraNet® Plus is WHO prequalified pyrethroid-PBO mixture 150 dernier net made of monofilament high density polyethylene (HDPE). It is incorporated with a mixture of alpha-cypermethrin at 6.0 g of active ingredient/kg and Piperonyl Butoxide (PBO) at 2.2 g of active ingredient/kg. It has a mesh size of 20 holes/cm^2^ and a fabric weight of 45 g/m^2^.DuraNet® is a WHO prequalified standard pyrethroid-only 150 dernier net also made of mono-filament high density polyethylene (HDPE). It is incorporated with alpha-cypermethrin at 5.8 g of active ingredient/kg. It has a mesh size of 20 holes/cm2 and a fabric weight of 45 g/m^2^. DuraNet® will serve as the reference net against which DuraNet® Plus will be compared.

DuraNet® Plus and DuraNet® are manufactured by Shobikaa Impex pvt Ltd (Karur, Tamil Nadu 639,006, and India).

### Study setting

The study will be conducted in selected malaria endemic villages in 3 different countries across sub-Saharan Africa: Benin, Cameroon and Tanzania. The countries have been selected to provide a suitable representation in the different regions in the area, West (Benin), Central (Cameroon) and East (Tanzania) Africa. Villages have been selected based on road accessibility, willingness to participate, availability of enough households, history of high ITN usage and proximity to the laboratory and insectary facilities of the participating institutional partners. A description of study area chosen for each country is provided in Table 1 below:

**Table 1 Tab1:** Description of study sites in Benin, Cameroon and Tanzania

Characteristics	Benin	Cameroon	Tanzania
Study villages	Agonkanme, Zantata Centre, Doutin and Agondokpoe	Ekoumeyeck and Agonfeme	Kibaoni, Magila, Misongeni and Ubembe
Estimated population size	~ 11,000	~ 6000	~ 7000
District	Zakpota District in Zou Department	Mbalmayo Districts in Central Region	Muheza district in Tanga Region
Geographical Coordinates	Latitudes 7° 13′ 49″ North Longitudes 2° 12′ 55″ East	Latitude: 3° 31′ 12″ North, Longitude: 11° 30′ 44″ East	Latitude: 5° 10′ 0.012" South. Longitude: 38° 46′ 59.988" East
Climate	Tropical humid climate Annual rainfall 1003.4mm and temperature of 27.1°C	Tropical savannah climate with wet and dry season. Annual rainfall 2402.8mm and temperature 26.5°C	Tropical savannah climate with wet and dry season Annual rainfall 293.6mm and temperature 23.7°C
Main vector population	*Anopheles gambiae sl.* resistant to pyrethroids	*Anopheles gambiae sl.* and *Anopheles funestus* resistant to pyrethroids	*Anopheles gambiae ss.* and *Anopheles funestus* resistant to pyrethroids
Typical economical activities	Agriculture and livestock	Agriculture, fishing and livestock	Agriculture, and livestock

### Study design outline

The study will be conducted in a minimum of 1800 households in each country to be randomly assigned to the two study arms. Nets will be distributed to each household and followed prospectively. Before net distribution, a baseline census will be carried out in the selected study villages to collect demographic information and socio-economic characteristics of the participating households. This will be followed by a net distribution campaign after which a series of follow-up surveys will be performed to assess adverse events, ITN survivorship, fabric integrity, insecticidal efficacy and chemical content over a period of 36 months. Figure 1 provides a summary of the surveys and the different studies to be performed at each timepoint.

**Fig. 1 Fig1:**
[figure not shown]
Flow chart of trial activities and outputs for monitoring the physical and insecticidal durability of DuraNet Plus in Benin, Cameroon and Tanzania. *Two cohorts of nets will be followed per study arm; cohort 1 nets will be assessed for ITN attrition and fabric integrity while cohort 2 nets will be withdrawn (and replaced) and assessed for bioefficacy and chemical content*

### Randomisation, blinding and sample size calculations

Households will be the unit of randomisation of this study. Participating households will be blinded to the type of ITN they received while data collectors will be blinded to the allocation of households to the study arms. Study nets (DuraNet® Plus and DuraNet®) will be identical in appearance. Two cohorts of nets of each ITN type will be followed; cohort 1 to assess ITN survivorship, attrition and Fabric integrity and cohort 2 for nets to be withdrawn for assessment of bioefficacy and insecticide content. A sample size of 510 households per study arm was found sufficient to detect a 7 points difference in ITN functional survival rate over 3 years between households receiving DuraNet® Plus and those receiving DuraNet® with 80% power, assuming a baseline 3-year survival rate of 25%. This sample size was increased by 100 households to account for loss to follow up over time. To account for nets to be withdrawn for bioefficacy studies, hut trials and insecticidal content, an additional 310 households per arm will be included in the study, hence a total of 920 households will be recruited per study arm at each site. It is estimated that about 3 nets will be required per household therefore the study will require 2,760 nets of each ITN type at each study site.

### Community sensitisation and baseline census

A series of community sensitisation meetings will be held in selected villages in each study site prior to the baseline surveys to ensure community participation. The study procedure and its objectives will be explained to leaders of all participating villages to ensure their cooperation with the study team. The meetings will be conducted in the local language of each community to ensure full participation. After the community sensitisation meetings, a baseline census will be conducted in all consenting households in the selected villages for each study site using a structured questionnaire. The census will provide a framework for allocation of study nets and for sampling at follow-up. The following information will be recorded: name of the village, name of the head of the household, number of household members with details of adults and children living in the house, number of nets already in the household, number of sleeping places and the global positioning system (GPS) coordinates will be recorded to assist in identifying houses during follow-up. Each house will be assigned a unique identifier which will be marked on the door of the house during the survey using indelible ink.

### ITN distribution and net master lists

The baseline census data will be used to randomly allocate households to each study arm using a random number generation scheme. The study team will then visit all participating households to provide vouchers for collection of study ITNs at a central point in each village. Where possible, households will be visited door-to-door to ensure that they receive their allocated net. Each ITN will be marked with a unique identifier before being provided to the household. The unique identifier will contain the household number, a unique number for the ITN, the ITN type and the cohort (cohort 1 and 2) to which the net has been assigned. Using these unique identifiers, net master lists will be generated, and these will contain a unique identification for each study net available in each household and separated by cohort to avoid any risk of destructive sampling of nets from households in cohort 1. As described previously, nets in the cohort 1 master list will be followed for attrition and fabric integrity while nets in the cohort 2 master lists will be withdrawn (and replaced with new nets of same type) for bioefficacy and insecticidal content studies.

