### Follow up surveys

#### Follow-up for ITN hang-up and adverse events

Between 1 week and up to 1 month post-distribution, sleeping places in houses in the net sampling lists (cohort 1 and cohort 2) will be observed to ensure that study nets have been set up. Where necessary, study teams will assist participants in hanging up their nets. The nets available in the house will also be checked to ensure that they match with what is available in the net sampling list which was generated after distribution and corrections will be made as necessary. During these visits, householders will be encouraged to use the study nets over any other nets available with them. Using a questionnaire, the adverse effects related to net usage will be investigated in 30 randomly selected households in each study arm at each study site. Heads of households will be questioned on any perceived adverse events including sneezing, itching, headache, numbness, eye discharge, any unpleasant smells and nausea in line with WHO guidelines. Participants will be advised to seek medical care from the nearest health facility should the symptoms persist.

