#### Follow-up for ITN attrition

Net attrition rate in households will be measured by recording the physical presence of the net at 6-, 12-, 24- and 36-months post ITN distribution. All households in cohort 1 will be visited and nets assessed for attrition at each timepoint by recording the physical presence/absence of each net attributed to the household. Where a net is not found, the householder will be questioned about the reason for the loss of the net e.g. given away, sold, stolen, worn out and disposed of etc. Any study nets which have never been used, will be recorded and excluded from the analysis. ITNs lost due to wear and tear will be considered as lost due to attrition, and those lost because they were stolen, sold or given away to others, will be considered as lost to follow-up. During these surveys, a questionnaire adapted from WHO guidelines will be used to collect data on the number of washes and washing practices for the nets found in each household. The household surveys will be conducted by an experienced socio-anthropologists.

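### The identifier marked on each net includes the ITN type, which conflicts with the stated blinding of households and data collectors

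*Protocol article*

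**What the plan says.** The section Randomisation, blinding and sample size calculations makes two statements about blinding: "Participating households will be blinded to the type of ITN they received while data collectors will be blinded to the allocation of households" to the arms, and "Study nets (DuraNet® Plus and DuraNet®) will be identical in appearance". The second is the only means of blinding that the article gives.

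The section ITN distribution and net master lists says: "Each ITN will be marked with a unique identifier before being provided to the household". It then lists the content of that mark: "The unique identifier will contain the household number, a unique number for the ITN, the ITN type and the cohort". It does not say whether the type is in clear text or coded, or who would hold a key.

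Field staff use the identity of the nets. At the hang-up visit, one week to one month after distribution, "The nets available in the house will also be checked to ensure that they match with what is available in the net sampling list". The same section collects a self-reported outcome: "Heads of households will be questioned on any perceived adverse events". Later surveys record the presence of each net attributed to a household and ask why a net is missing. Nets lost to wear count as attrition, while "those lost because they were stolen, sold or given away to others, will be considered as lost to follow-up". Data management and analysis excludes that second group from functional survival. Under Follow-up for ITN fabric integrity, the survey team counts and sizes the holes in each cohort 1 net.

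**The concern.** Blinding that rests on the nets looking the same does not survive a visible mark that tells them apart. If staff or householders know the arm, or can group nets by arm, their reports and judgements can differ between arms for reasons unrelated to the nets. Randomisation does not remove that bias.

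The most exposed item is the reason for loss. It is a verbal report, and it decides whether a missing net counts as a failure or leaves the functional survival analysis. Functional survival is the outcome on which the sample size is based. Perceived adverse events are also self-reported. Hole scoring is a structured count in centimetre size classes, so it leaves less room for judgement, but an assessor still does it with the net in hand.

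**Working it through.** **1. The statements side by side.**

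| Section of the protocol article | Statement | Consequence |
|---|---|---|
| Randomisation, blinding and sample size calculations | Households and data collectors blinded; nets look the same | Nothing visible on a net may show its arm |
| ITN distribution and net master lists | The mark on the net contains the type | Something on the net does show its arm |
| Follow-up for ITN hang-up and adverse events | Nets in the house compared with the list | Data collectors use the net's identity |

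**2. The two ways to read the type field.**
- *Legible type:* householders and data collectors can both read it, so neither group is blinded.
- *Fixed two-level code:* householders may not learn the product. Data collectors still see two groups of nets, and learning the meaning of the code once reveals every net.

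**3. Missing nets.** A lost net has no mark to read. However, households are randomised as units and are expected to hold about 3 nets each. One remaining net in the house, or a list entry carrying the same identifier, shows the arm while the reason for loss is being asked.

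**4. The plan's own figures, for context.** The sample size is 510 households per arm for a 7-point difference from 25%, with 80% power. Alpha and sidedness are not stated. With proportions 0.25 and 0.32 (mean 0.285) and an assumed one-sided 5% test:

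n = [1.645·√(2·0.285·0.715) + 0.842·√(0.25·0.75 + 0.32·0.68)]² / 0.07² ≈ 514, within 1% of 510.

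A two-sided 5% test gives 652. The blinding point does not depend on either figure.

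**5. Illustration of size.** The misreporting rates below are assumptions and do not come from the documents. Assume that true survival is 25% in both arms, so 75 of 100 nets fail. Let L be the number of failed nets per 100 that are physically lost, and m the share of those lost nets recorded in one arm as given away and so excluded. As a simple proportion,

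apparent survival = 25 / (100 − m·L).

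- All failures are lost nets (L = 75):
  - m = 10%: 25/92.5 = 27.0%
  - m = 20%: 25/85 = 29.4%
  - m = 30%: 25/77.5 = 32.3%
- Half the failures are torn nets still present (L = 37.5), m = 20%: 25/92.5 = 27.0%.
- To create the whole 7-point difference, 25/(100 − m·L) = 0.32 requires m·L = 100 − 25/0.32 = 21.9. That is m = 21.9/75 = 29% if all failures are lost nets, or 21.9/37.5 = 58% if half are.

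**The case against.** The article says that the identifier contains the type, not that the type is printed in clear. An arbitrary code would keep householders unaware of the product, and a condensed article may leave coding rules and key-holders to the full protocol. This stands as far as it goes: a reader might infer that blinding certainly fails for everyone, and the documents do not establish that for householders. It does not rescue the statement about data collectors, because a constant two-level code still sorts nets and households by arm.

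The outcomes are also less open to judgement than they may seem. Presence of a net is objective, holes are counted by panel and size class, and the reason for loss is the householder's answer. That is why hole scoring is placed below the self-reported items. It does not protect the reason for loss.

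Two further inferences should be avoided.
- A reader might conclude that bioassay and hut scoring are unblinded too. The article claims blinding only for households and data collectors, and does not say that the mark stays with cut pieces or that withdrawn nets are not recoded. Nothing there is contradicted.
- A reader might suppose that the label is read at every visit. The article describes matching nets to the list only at the hang-up visit. Later reading is plausible but not stated.

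Finally, some staff need type information, since withdrawn cohort 2 nets must be replaced like for like, and cohort must stay visible so that cohort 1 nets are not withdrawn by mistake. Both needs are legitimate and shape the remedy. Neither requires the survey team to see the type.

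**Conclusion.** The two sections conflict. Followed as written, the marking procedure undermines a blinding property that the article claims. For data collectors this holds whether the type is legible or a fixed code. For householders it holds if the type is legible, which the article neither states nor rules out.

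The exposed outcomes are perceived adverse events, the reported reason for net loss and, to a lesser degree, hole scoring. The documents give no basis for estimating how much bias would result. The illustration shows only that misreporting 20% of lost failed nets in one arm would move apparent survival by 2.0 to 4.4 points, depending on how many failures are torn nets still in the house. That compares with a design difference of 7 points. It is not a forecast, and the conflict stands without it.

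**What to change.** - **Identifier.** Remove ITN type from the identifier used in the field. Household number, net serial number and cohort are enough to find a net and to protect cohort 1 from withdrawal.
- **Linkage.** Hold the link from serial number to type in a restricted file, used by someone outside the survey team. That person also arranges the same-type replacements for withdrawn cohort 2 nets, and those replacements can carry a type-free mark.
- **Remaining surveys.** Status of study reports that nets are distributed, that the 6-month round is complete and that further surveys are under way. For those, use working lists and forms without the type. If the mark on the nets itself shows the type, this helps only in part.
- **Disclosure.** State what was actually marked on the nets, whether the type was coded, and who held the key. If it was legible, correct the blinding statement and report the field assessments, including those already done, as not blinded. If it was a fixed code, say that data collectors could group nets by arm.

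The cost is one linkage file, revised lists and forms at three sites (electronic in Benin, paper in Cameroon and Tanzania) and a few sentences of text. No extra nets or visits are needed.
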